### Trial duration

Patient recruitment is planned to be completed after 24 months. Patients will be monitored for three years after study entry. The total duration of the trial is estimated to be five years. Recruitment will begin in April 2013.

### Assessment of therapeutic efficiency

Assessments including patient history, physical exam, CT of neck, chest and abdomen, bone marrow biopsy and serological tumor markers are scheduled before, during and after treatment and during follow up. Response is evaluated in accordance with the Cheson Criteria [9]:

• Complete response (CR) is the complete disappearance of all detectable evidence of disease on CT, and all disease-related symptoms, and normalization of biochemical abnormalities, and normal bone marrow biopsy (BMB). Previously involved nodes on CT more than 1.5 cm in their greatest axial diameter must regress to less than 1.5 cm, and previously measured nodes of 1.1–1.5 cm must decrease to less than 1 cm.

• CRu (uncertain) corresponds to CR criteria but with a residual mass more than 1.5 cm in greatest axial diameter that has regressed by more than 75%.

• Partial response (PR) is at least 50% reduction in the sum of the product of the greatest diameters (SPD) of the six largest nodes with no increase in the size of other nodes and no new sites of disease. Splenic and hepatic nodules must regress by at least 50% in the SPD.

• Stable disease (SD) is less than a PR but is not progressive disease. Progressive disease (PD) is more than 50% increase in the sum of the product of the greatest diameters of any previously abnormal node, or appearance of any new lesions during or at the end of therapy.

• Relapsed disease (RD) is the appearance of any new lesion or increase in size of more than 50% of previously involved sites or nodes in patients who achieved CR or CRu.

PET-data will be collected if available upon discretion of the individual physician.

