### Statistical design

In phase I of the study, a 6 + 6 standardized design is chosen to establish the MTD of the investigational product (temsirolimus). A maximum of 48 patients can consequently be included into this phase. In phase II of the study, 40 patients will be included, receiving two to four cycles of the full target dose of temsirolimus in combination with R-DHAP, as established in phase I of the trial. The number of cycles will depend on the evaluation of activity and toxicity of the regimen by the investigator in each individual patient. Based on published data on rituximab in combination with DHAP, a response rate of at least 60 to 65% (40% CR and CRu) can be expected. The study will be terminated if the number of non-responders exceeds a critical value determined by Wald´s Sequential probability ratio test. In both phases of this trial explorative statistics are used to calculate remission and response rates. Median progression free survival, overall survival etc. are calculated by the Kaplan and Meier method. Adverse events will be classified according to MedDRA terminology. The frequency of adverse events will be calculated, and there will be further analyses to determine their seriousness, intensity, duration, relationship to trial treatment, actions taken and clinical outcome. Patients with and without consolidating high dose therapy and autologous stem cell transplantation will be analysed separately.

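### A residual of exactly 1.5 cm is neither CR nor CRu, so a smaller residual can get a worse class, and the measure for the 75% CRu regression is not named

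*Protocol article*

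**What the plan says.** All class definitions stand in the protocol article under Assessment of therapeutic efficiency, which refers to the Cheson criteria by citation and then prints its own limits.

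- CR, larger nodes: "Previously involved nodes on CT more than 1.5 cm in their greatest axial diameter must regress to less than 1.5 cm".
- CR, smaller nodes: "previously measured nodes of 1.1–1.5 cm must decrease to less than 1 cm".
- CRu: the CR criteria, but with "a residual mass more than 1.5 cm in greatest axial diameter that has regressed by more than 75" per cent.
- PR: "at least 50% reduction in the sum of the product of the greatest diameters (SPD) of the six largest nodes", with no growth elsewhere and no new sites.
- SD: anything short of PR that is not progression.

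Under Statistical design, the article expects from published R-DHAP data that "a response rate of at least 60 to 65% (40% CR and CRu) can be expected", and says that in both phases "explorative statistics are used to calculate remission and response rates". Phase II enrols 40 patients. Its primary objective is ORR, and its stopping rule counts non-responders.

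**The concern.** Response classes should be ordered: a smaller residual from the same baseline should never earn a worse class. They should also leave no result without a class that fits it. The CR limit stops just below 1.5 cm and the CRu limit starts just above it, so the value between them drops to PR or lower. CT diameters are recorded in discrete steps and 1.5 cm is the cut-point itself, so the value can be expected to occur.

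The second weakness is in the same sentence. CRu depends on a 75% regression, but the scale is not given. Two assessors following the text in good faith could class the same scan differently.

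At stake is the split between CR/CRu and PR. It feeds the remission rate that readers will set beside the 40% expectation. It also decides whether the article's definition of relapsed disease, which is limited to patients who reached CR or CRu, applies to a patient.

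**Working it through.** **Inputs from the article.** CR: residual below 1.5 cm for nodes above 1.5 cm at baseline. CRu: residual above 1.5 cm and regression above 75%. PR: at least 50% fall in the product of diameters. Expected CR/CRu 40%; phase II n = 40.

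**Assumptions for the illustrations.** One node decides the class, both diameters shrink in proportion, and all other CR conditions are met. With baseline diameter b and residual r, the fall in diameter is 1 − r/b and the fall in product is 1 − (r/b)².

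**The plan's figure.** 0.40 × 40 = 16 patients expected in CR or CRu. This is a literature expectation; nothing in the article derives it, so there is no formula to reproduce.

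**Step 1: the boundary.** Baseline 7.0 cm:

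| Residual | Fall in diameter | Fall in product | CR (<1.5)? | CRu (>1.5 and >75%)? | Class |
|---|---|---|---|---|---|
| 1.6 cm | 77.1% | 94.8% | no | yes, on either scale | CRu |
| 1.5 cm | 78.6% | 95.4% | no | no, size not above 1.5 | PR |
| 1.4 cm | 80.0% | 96.0% | yes | – | CR |

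The order is broken whichever scale the 75% uses.

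**Step 2: when the reversal can occur.** A residual of 1.6 cm must itself qualify as CRu. On diameter this needs b > 1.6/0.25 = 6.4 cm. On the product it needs b > 1.6/√0.25 = 3.2 cm. Below these baselines 1.5 cm still fails CR, but the 1.6 cm neighbour fails CRu too, so the order is not reversed.

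**Step 3: the unnamed measure.** A 75% fall in diameter is a fall of 1 − 0.25² = 93.75% in product. A 75% fall in product is a fall of 1 − √0.25 = 50% in diameter. Two examples:

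- 5.0 to 1.6 cm: diameter falls 68%, product 89.8%. PR on diameter, CRu on product.
- 5.0 × 4.0 to 2.2 × 1.8 cm: product 20.0 to 3.96 cm², a fall of 80%; diameter falls 56%. Again PR on diameter, CRu on product.

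**Step 4: effect on ORR.** A residual of 1.5 cm still reaches PR if (1.5/b)² ≤ 0.5, that is b ≥ 1.5/√0.5 = 2.12 cm. Below about 2.1 cm it falls to SD. For example, 1.8 × 1.4 to 1.5 × 1.2 cm goes from 2.52 to 1.80 cm², a fall of 29%. Such nodes are admitted, since Patient selection accepts a mass just above 1.5 × 1.0 cm. Only these patients would change from responder to non-responder.

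**Step 5: possible size of the boundary loss.** The documents give no distribution of residual sizes. Let s be the assumed share of CR/CRu patients recorded at exactly 1.5 cm; the reported rate is 40% × (1 − s).

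| s (assumed) | Reported CR/CRu | Patients of 40 |
|---|---|---|
| 0% | 40.0% | 16.0 |
| 2% | 39.2% | 15.7 |
| 5% | 38.0% | 15.2 |
| 10% | 36.0% | 14.4 |

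**The case against.** The strongest reply is that this is a one-point wording gap in a condensed article that defers to cited criteria, that it touches an exploratory rate, and that no test, threshold or stopping rule uses CR/CRu. Much of that stands, and it limits the weight of the point. It does not remove it: the article chose to print the limits, and the printed limits give a wrong order.

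Three stronger readings are tempting, and the documents do not support them.

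- A reader might infer that the 75% is tied to diameter, because that is the only dimension in the sentence. Grammatically, the diameter qualifies the 1.5 cm size, and it is the mass that has regressed. The measure is unnamed, not fixed to diameter.
- A reader might then infer a large undercount, with perhaps 8 to 13 patients reported in CR/CRu instead of 16 of 40. That needs invented node sizes. It also needs assessors to use diameter while the 40% rests on the product. The article shows neither, nor how the published studies behind the 40% handled these limits. If they applied the same rules, the comparison is not biased.
- A reader might see the same hole at 1.0 cm, since nodes of 1.1 to 1.5 cm must fall below 1 cm. A residual of 1.0 cm fails CR, but so does every larger residual from such a node. The order is kept, so this is an ordinary cut-off.

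**Conclusion.** The point holds in a limited form. Exactly 1.5 cm belongs to neither CR nor CRu, and a larger residual can therefore receive the better class. This follows from the printed inequalities alone. The missing measure for the 75% is a second, related ambiguity that changes the class of some masses.

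The boundary gap can only lower the CR/CRu rate. Its size cannot be derived from the documents and is probably small: under two patients of 40 even if a tenth of CR/CRu patients fell on the boundary. The direction of any effect from the 75% is not established. ORR and the non-responder rule are largely unaffected; the exception is a patient whose deciding node was below about 2.1 cm at baseline, assuming proportional shrinkage. This is a minor but clear correction.

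**What to change.** Under Assessment of therapeutic efficiency:

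1. Assign a residual of exactly 1.5 cm to one class so that CR and CRu adjoin, for example by letting CR include 1.5 cm. Check the choice against the cited response criteria, which are not shown here.
2. Name the measure for the CRu regression (greatest diameter or product of diameters), again checked against the cited criteria. State it on the same scale as PR if that is what is meant.
3. Carry both changes into the response derivation, and settle them before responses are classified.

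The cost is two wording edits and a matching line in the derivation. No new scans, assessments or patients are needed. The 1.0 cm limit need not change on this account.

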### Quality assurance program

Quality assurance, database management, monitoring and reporting is performed by the Interdisciplinary Centre for Clinical Trials (IZKS) at the University of Mainz.

## Discussion

The STORM trial evaluates the safety, feasibility and activity of salvage therapy consisting of the mTOR inhibitor temsirolimus added to standard therapy of rituximab and DHAP for the treatment of patients with relapsed or refractory DLBCL. It also might identify predictive markers for this treatment modality.
